### Interventions

The trial will compare 2 different policies for RBC transfusion, “restrictive” and “liberal”. All eligible patients admitted to a participating site should be transfused in accordance with the randomized transfusion policy.

#### Restrictive Transfusion Policy (RBCs Transfused When Hb ≤ 8 g/dL)

If the Hb value is recorded as ≤ 8.0 g/dL, RBCs should be transfused with the aim of keeping the Hb range between 8.1 and 10.0 g/dL. Further RBC transfusions should only be administered if the Hb value decreases to a value of 8.0g/dL or less.

#### Liberal Transfusion Policy (RBCs Transfused When Hb ≤ 10 g/dL)

If the Hb value is recorded as ≤ 10.0 g/dL, RBCs should be transfused with the aim of keeping the Hb range between 10.1 and 12.0 g/dL. Further RBC transfusions should only be administered if the Hb value decreases to a value of 10.0 g/dL or less.

In both intervention arms the number of RBC units transfused and the timing of repeat Hb measurements will be decided by the caring clinician. Any transfusion(s) required as part of the policy should be administered within 24 hours of obtaining the Hb result.

#### Clinician Discretion to Transfuse in Contravention of the Allocated Policy

All clinicians will have the discretion to transfuse, or not to transfuse, in contravention of the allocated policy for any patient admitted with AUGIB. Any clinician who deviates from the policy will be asked to provide the reason(s) for doing so on a Case Report Form. This is not designed to challenge the clinician’s judgment, but rather to identify patient subgroups, which may not be feasible to recruit into the planned phase III trial. Possible reasons for additional transfusions outside of the protocol could include periods of further bleeding or hemodynamic instability.

### Outcomes

The study will collect a range of feasibility outcome measures and clinical outcome measures.

Feasibility outcome measures for each treatment arm include:•The proportion of eligible patients who provide consent.•The proportion of patients who are ineligible due to need for immediate transfusion.•Protocol adherence, which includes:1.Overall adherence: the proportion of Hb counts for each patient where no deviation occurred. This will be averaged across all patients.2.Adherence per Hb count: the overall proportion of Hb counts where no deviation occurred.3.Adherence per patient: the proportion of enrolled patients for whom no transfusion deviation occurred.•Selection bias: As the study is open-label, all clinicians will be aware of their hospital’s transfusion policy, resulting in the possibility of selection bias. The following outcomes will be compared between the 2 interventional arms in order to investigate this:oAge, shock, Hb at baseline, clinical Rockall score, Blatchford score, and the number of major comorbidities for consented patientsoThe difference in the baseline Hb, Rockall and Blatchford scores of consented vs. those not consented•The number of RBC units transfused•The proportion of patients receiving at least one RBC transfusion.•The mean Hb over the first 7 days after admission•The mean Hb over the entire study period (i.e. up to discharge/death/28 days)•The mean Hb on discharge (the last recorded Hb prior to discharge will be used)

Clinical outcome measures include:•Further bleeding up to day 28: further bleeding is a composite outcome that includes persistent bleeding and recurrent bleeding. Recurrent bleeding should initially be suspected in the event of any combination of the following: fresh hematemesis, continuous melena, or aspiration of fresh blood from a nasogastric tube, with a pulse rate of > 100 bpm, a fall in systolic blood pressure of > 30 mm Hg or a drop in Hb of > 2g/dL in the preceding 24 hours.•Further bleeding up to hospital discharge•All-cause mortality up to day 28.•All-cause mortality up to hospital discharge•Therapeutic intervention at the index endoscopy•Surgical or radiological intervention to control bleeding up to death/discharge•Proportion of patients experiencing the composite end point of thromboembolic and ischemic events up to Day 28. This is composed of myocardial infarction, stroke, pulmonary embolus, DVT, and acute kidney injury. Each component will also be assessed individually.•Proportion of patients experiencing the composite end point of thromboembolic and ischemic events up to hospital discharge•Acute transfusion reactions up to death/discharge. This is defined as a reaction occurring at any time up to 24 hours following a transfusion of a blood component.•Infection up to day 28. This is defined as any infection necessitating a prescription for antibiotic treatment for a minimum of 5 days, provided the prescription is received before or on day 28•Infection up to hospital discharge•Length of hospital stay•Health related quality of life at Day 28 (using EuroQol EQ-5D).•Serious adverse events up to day 28.

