### Design and Setting

TRIGGER is a pragmatic, cluster randomized feasibility trial comparing 2 different RBC transfusion strategies in patients admitted with AUGIB. Each participating center will be randomly allocated to one of 2 transfusion policies, and all eligible patients in a centre will be treated according to the allocated transfusion policy. The trial will recruit in 6 academic centers in the UK. Both feasibility and clinical outcome measures will be collected. Feasibility measures include recruitment rate, adherence to the transfusion policy, the difference in Hb, and RBC exposure between the restrictive and liberal transfusion policies and evidence of selection bias. Clinical outcomes include further bleeding, mortality, need for therapeutic endoscopy, need for surgery or radiological intervention to control bleeding, thromboembolic, and ischemic events, infections, transfusion reactions, and an assessment of quality of life at day 28 (EuroQol EQ-5D). Data will also be gathered to identify factors leading to contravention of the transfusion policy, and to enhance estimates of the intraclass correlation coefficient (ICC) to inform the sample size calculation for a phase III cluster randomized trial. The full trial protocol is available on the dedicated trial Web site: http://www.trigger.nhsbt.nhs.uk/.

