### Randomization of Clusters

Widespread consultation was conducted amongst clinical stakeholders in each potential center to ensure a willingness to be randomized to either transfusion policy and agreement to implement the allocated policy on a hospital wide level. Centers will be randomized using permuted blocks without stratification or matching, in order to ensure an equal number of centers are assigned to each transfusion policy. Recruitment of patients will operate for 6 months in total in each center.

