### Sample Size

As this is a feasibility study, no formal sample size calculation was undertaken to determine the number of patients required based upon a primary end point. Using information on the number of admissions with AUGIB at each participating centre, we estimated 1062 eligible patients would present over the course of 6 months. Assuming an 80% consent rate, this would give 849 patients enrolled in total.

This feasibility study will also help to inform the sample size calculation for the definitive phase III trial by allowing estimates of the rate and ICC for further bleeding, which is likely to form the primary outcome of the phase III trial.

TRIGGER is not powered on the end-points of further bleeding or mortality. However safety is being monitored by review of serious adverse events by an independent data monitoring committee. Any large imbalances between treatments that suggest harm would influence the feasibility of a larger follow on trial, as is the case in all early phase studies.

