### Data Collection

#### Screening Log

A daily screening log of all patients admitted with AUGIB will record the total number of admissions, the number meeting eligibility criteria and eligible patients enrolled in each hospital. Anonymized, baseline clinical characteristics for each patient will be recorded.

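### The selection-bias checks leave age, shock and comorbidity confounded with hospital case-mix, and do not isolate selection at the exclusion for immediate transfusion

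*Protocol article*

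**What the plan says.** The Outcomes section of the protocol article notes that clinicians know their hospital's policy, so selection bias is possible. It continues: "The following outcomes will be compared between the 2 interventional arms in order to investigate this". Two items follow, neither ranked above the other:

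- (a) six baseline characteristics of consented patients: age, shock, Hb, clinical Rockall score, Blatchford score and number of major comorbidities;
- (b) the difference between consented and non-consented patients, for baseline Hb, Rockall and Blatchford only.

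The same list separately reports, for each arm, the proportion of eligible patients who consent and the proportion ineligible because they need immediate transfusion.

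On design: "The trial will recruit in 6 academic centers in the UK", and "Centers will be randomized using permuted blocks without stratification or matching", so that there are three hospitals per arm. Data Analysis specifies cluster-level summaries. The Screening Log section covers every patient admitted with AUGIB and adds: "Anonymized, baseline clinical characteristics for each patient will be recorded".

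**The concern.** Comparison (a) measures two things at once: any selection, and the chance difference in case-mix between three hospitals and three others. With allocation by "permuted blocks without stratification or matching", nothing in the design restrains the second part, and no analysis of consented patients alone can separate the two. A null result is weak reassurance, and a positive one may reflect only which hospitals fell in which arm. For age, shock and comorbidities this is the only comparison named.

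Selection can also occur before consent. Under Eligibility Criteria, the responsible clinician, who knows the policy, decides whether a patient is excluded as needing immediate transfusion. Comparison (b), on its natural reading, starts among eligible patients and so comes after that decision.

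Evidence of selection bias is a named feasibility measure, and the trial exists to inform the design of a phase III trial. A check that cannot be interpreted could wrongly reassure or wrongly count against the cluster design.

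**Working it through.** **Inputs from the article (Sample Size, Design and Setting, Randomization of Clusters).** 1062 eligible patients, 80% consent, 849 enrolled, six hospitals, three per arm.

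Reproducing the plan's figure: 1062 × 0.80 = 849.6, against 849 stated. With equal hospitals this gives 1062/6 = 177 eligible, 849/6 = 141.5 enrolled and 213/6 = 35.5 not consented per hospital.

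**Assumptions not in the article.** ICC of baseline variables 0 to 0.10; a two-sided 5% t-test on six hospital values (4 df); a normal covariate; selection in one arm only.

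**Extreme selection at consent.** Suppose one arm's non-consenting 20% are exactly its most extreme, while non-consent in the other arm is random.

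- The normal density at the 80th percentile is 0.280.
- The enrolled mean shifts by 0.280/0.8 = 0.35 SD.
- The gap between consented and non-consented means is 0.280/0.8 + 0.280/0.2 = 1.75 SD.

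**Comparison (a).** SE = √(2/3 × [ICC + (1 − ICC)/141.5]), with power from the noncentral t.

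| ICC | SE (in SD) | Missed |
|---|---|---|
| 0 | 0.069 | 4% |
| 0.01 | 0.106 | 31% |
| 0.02 | 0.134 | 49% |
| 0.05 | 0.194 | 72% |
| 0.10 | 0.266 | 82–83% |

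Simulation gave 31%, 50% and 73% at ICC 0.01, 0.02 and 0.05. If the arms select to the extreme in opposite directions (0.70 SD apart), the miss falls to 0.3% at ICC 0.01 and 23% at 0.05.

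**Comparison (b), same scenario.** The hospital effect cancels. A conservative SE is √(2/3 × [1/141.5 + 1/35.5]) = 0.153, against a gap of 1.75. Power is about 100%, and 94% if the gap itself varies between hospitals with SD 0.4.

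**Selection at the exclusion step.** One arm excludes exactly its most extreme patients, the other excludes the same share at random, and consent is random at 80%. The article does not give the share excluded, so 10% and 20% are assumptions. There were 4,000 simulated trials per row; a separate run agreed to within about a percentage point.

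| Excluded | ICC | Power (a) | Power (b) | Enrolled v all screened, within hospital |
|---|---|---|---|---|
| 10% | 0.01 | 30% | 5% | 99% |
| 10% | 0.05 | 12% | 5% | 99% |
| 20% | 0.01 | 70% | 5% | 100% |
| 20% | 0.05 | 27% | 5% | 100% |

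Comparison (b) rejects at its false-positive rate.

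**A milder version.** Both arms exclude on a severity score correlated 0.7 with the characteristic, but one arm excludes twice the share of the other (20% v 10%, or 40% v 20%). Over ICC 0.01 and 0.05, with 6,000 trials each, power was 8–43% for (a), about 5% for (b), and 34–79% for enrolled v all screened. When both arms applied one common severity threshold, so that there was no selection, the last contrast rejected 4–5% of the time.

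**The case against.** The strongest reply is that the plan already contains the right tool. Comparison (b) is a within-hospital contrast and stands beside (a) without being subordinate to it. A reader might infer that selection bias is judged mainly by the confounded comparison, and that the plan therefore misses a third to 70% of even extreme selection. The article does not support that. It ranks neither comparison, the miss rate belongs to (a) alone, and (b) detects the same consent-step scenario almost always for Hb, Rockall and Blatchford. This part of the reply stands in full.

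A reader might also quote an SE of 0.03–0.045 SD for enrolled minus all patients as a gain over the plan. With 80% enrolled, enrolled minus all eligible is 0.2 times the consented v non-consented difference: 0.2 × 0.153 = 0.031, or 0.2 × √(2/3 × [1/141.5 + 1/35.5 + 0.2²]) = 0.045 with between-hospital variation of SD 0.2. It is the plan's own contrast rescaled, has the same power, and applies to eligible patients only.

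Two further replies stand in part. The proportion ineligible for immediate transfusion is reported per arm, so that step is not ignored, but a proportion does not show who was excluded and it varies with hospital case-mix. Adding excluded patients to a contrast also brings back some case-mix, because they are excluded for severity. In the simulations this lowered power but did not inflate false positives under a common threshold.

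Finally, interpretation may be left to the analysis plan, which is not shown. The choice of comparisons, and of variables for each, is fixed in the article itself.

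**Conclusion.** The point holds in a limited form. For Hb, Rockall and Blatchford at the consent step, the plan is adequate. Two gaps remain.

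- Age, shock and number of comorbidities rest on a comparison that cannot separate selection from case-mix. Taken alone, it would miss loss of the most extreme 20% in one arm about 31% of the time at ICC 0.01 and 72% at 0.05. These figures depend on assumed ICCs, one-arm selection and a 5% test on 4 df; the article gives no ICC for baseline variables and names no test.
- Selection at the open-label exclusion for immediate transfusion is invisible to (b), appears in (a) only mixed with case-mix, and otherwise shows only as a per-arm proportion with the same weakness.

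The change is worth making because the data are already planned and the measure feeds the phase III decision. It does not call the trial's other outcomes into question.

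**What to change.** In the analysis plan:

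1. Keep the consented v non-consented contrast and extend it to all six listed characteristics, as far as the screening log holds them.
2. Add a second within-hospital contrast: enrolled patients v all screened new AUGIB admissions, including those excluded for immediate transfusion. Leave out existing inpatients who develop AUGIB.
3. Compare each contrast between arms using the six hospital-level values, with a 95% CI, and read the second beside the per-arm proportion ineligible.
4. Present the consented-only comparison as a description of case-mix, not as evidence for or against selection.

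The cost is a few lines of text and some extra analysis, with no new data collection for variables already logged. There are two downsides to state. Log entries for non-enrolled patients may be less complete, and some case-mix remains in the second contrast because patients are excluded for severity. The 0.03–0.045 SE should not be quoted for that contrast; its precision depends on the number excluded, which the article does not give.

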### Participant Screening and Selection

Potential trial participants will be identified from Emergency Departments (ED) or Medical Admissions Units (MAU) from September 2012 until February 2013. All eligible patients will be managed in accordance with the hospital’s allocated transfusion policy, from presentation up to discharge. This will be facilitated through extensive education of clinical staff in acute admission areas, display of treatment algorithms in relevant clinical areas and a simple flagging system in blood banks to remind doctors of the hospital’s transfusion policy whenever a transfusion request for AUGIB occurs. The trial research nurse/member of the research team will screen admission lists daily and will be encouraged to have a strong presence in the emergency admissions area(s) to ensure admissions with AUGIB are identified daily. All eligible patients will be approached as soon as possible after presentation with AUGIB to obtain informed consent. All patients who provide written informed consent for data collection and follow-up at Day 28 will count as enrolments to the study. A schema of enrolment procedures is outlined in Figure.

### Consent and Ethical Considerations

Cluster randomized trials (CRTs) pose unique ethical challenges [34]. Consent may be sought at a number of levels in CRTs including from a “guardian” of the cluster for randomization of the cluster to the intervention, and/or consent from individual participants [35,36]. The consent process for this study was carefully considered in consultation with clinicians and patients. Consent will be sought from relevant clinical stakeholders at each center to enable the hospital to be randomized to the transfusion policy, such that all eligible patients admitted with AUGIB are treated with that policy for the duration of trial. Individual eligible participants will be approached as soon as possible after hospital presentation, if appropriate to his/her clinical condition, to consent for use of their routine hospital data and follow-up at day 28.

It is anticipated that the vast majority of patients will have capacity to provide consent. However, some patients may lack capacity to provide consent or have fluctuating capacity; in these cases guidance is provided by the Mental Capacity Act (England and NI; 2005) and Adults with Incapacity Act (Scotland; 2000).

### Consumer Involvement

We formed a TRIGGER trial focus group comprising members of the Patient Panel from the John Radcliffe Hospital, Oxford. Some members of this group had suffered from AUGIB and had received blood transfusions in the past. We discussed with the panel the ethical issues involved in the consent process and the complexities involved in cluster randomization. Two face-to-face focus groups with 9 members of the panel were conducted and involved an educational seminar about AUGIB and clinical trials.

We used a mixture of both qualitative and quantitative methods of feedback and all participants completed an anonymous questionnaire. All participants supported (as indicated both in the discussion and anonymous feedback forms) the consent processes outlined. Specifically they unanimously supported the notion of automatic treatment of eligible patients with the hospital’s allocated transfusion policy without the need to obtain patient consent for the intervention, given the existing variation in transfusion practice we have demonstrated throughout the UK and the fact that both policies are within current practice. However, they stressed that all clinicians involved in the patient’s care should have the discretion to transfuse in contravention of the policy if they wish to do so, such that patient safety is not compromised. Members of the panel also helped to inform the content of the information sheets and consent forms. A similar process was conducted with a patient group through Age UK and the summaries of these meetings helped to inform our ethics application.

### Sample Size

As this is a feasibility study, no formal sample size calculation was undertaken to determine the number of patients required based upon a primary end point. Using information on the number of admissions with AUGIB at each participating centre, we estimated 1062 eligible patients would present over the course of 6 months. Assuming an 80% consent rate, this would give 849 patients enrolled in total.

This feasibility study will also help to inform the sample size calculation for the definitive phase III trial by allowing estimates of the rate and ICC for further bleeding, which is likely to form the primary outcome of the phase III trial.

TRIGGER is not powered on the end-points of further bleeding or mortality. However safety is being monitored by review of serious adverse events by an independent data monitoring committee. Any large imbalances between treatments that suggest harm would influence the feasibility of a larger follow on trial, as is the case in all early phase studies.

### Data Collection

#### Screening Log

A daily screening log of all patients admitted with AUGIB will record the total number of admissions, the number meeting eligibility criteria and eligible patients enrolled in each hospital. Anonymized, baseline clinical characteristics for each patient will be recorded.

#### Baseline Characteristics

Baseline clinical characteristics will be obtained from routine patient records and will include age, gender, presenting symptoms, routine physiological parameters, Rockall and Blatchford score [37] and use of anti-platelets/anticoagulants.

#### Laboratory and Transfusion Data

The date and time of all Hb measurements will be recorded as well as the first coagulation screen, liver function test, and biochemistry profile. All RBC transfusion episodes will be recorded including the Hb level prior to transfusion and the total number of RBC units transfused. The number of other blood components administered including fresh frozen plasma and platelets will be recorded.

#### Endoscopic and Pharmacological Data

Endoscopic data will include date and time of endoscopy, endoscopic diagnosis, stigmata of hemorrhage, and nature of therapeutic procedure. Pharmacological data will include use of proton pump inhibitors before and after endoscopy and the use of antibiotics and vasopressors for patients with variceal hemorrhage.

#### Day 28 Follow-Up

Day 28 follow-up will be conducted by telephone to assess a list of pre-defined clinical outcomes, quality of life (QoL), and resource use details. The patient’s primary care physician will first be telephoned to ascertain survival status before calling the patient. A telephone version of the EQ-5D questionnaire will be used to assess QoL. For patients who are still in hospital at Day 28 this will be conducted face-to-face.

### Data Management

All data will be recorded on paper case report forms. Centers will send copies of completed case report forms to the data manager at the NHS Blood and Transplant Clinical Studies Unit, where they will be entered onto a bespoke trial database designed using the MACRO v3.2 clinical trial software management system supplied by InferMed Limited.

